#### Cohort study

Potential study participants will be identified through the 3-months post-stroke standard telephonic clinical examination (mandatory clinical follow-up in Denmark). Patients will be pre-screened ahead of this examination in order to determine eligibility. During the standard telephonic clinical examination, the clinician will provide the eligible patients with a short oral information about the project and ask the person for oral consent allowing the research team to contact the patient to provide in-depth oral information. Patients consenting to later contact will be provided with verbal (telephonic) and written information about the project by a member of the research team. Should the potential participant wish it a family member/friend will be contacted and provided with the same oral and written information. If interested, participants will be asked to give their informed consent (through digital mail) for participation in the prospective cohort including access to patient records.

#### RCT study

Participants in the prospective cohort will be screened 6 months post-stroke to determine RCT-study eligibility, and stroke-affected individuals will be recruited and screened through municipal rehabilitation centres at 12 months post-stroke. If eligible and interested, a member of the research team will provide the participant with written and oral information regarding the project, and the same will be offered to a family member or friend, should the participant wish it. Participants will be offered a physical meeting and will be given at least 24 h to consider before signing the informed consent form. Should the participant wish to participate in the RCT, the informed consent form will be signed on the first day of testing before commencement of any testing procedures.

#### Retention, drop-outs, and discontinuation

Retention will be monitored and promoted by sending systematic reminders to participants regarding questionnaires. Data regarding reason for drop-out or discontinuation is collected and will be reported in the patient flow-chart. Discontinuation may occur 6 months post-stroke for individuals who have regained enough functional capacity to score 1–2 on the mRS or in cases of recurrent cardiovascular/cerebrovascular events (as per the exclusion criteria).

### Intervention

#### Training dosage

The training dosage for both INT and CON will be matched for total hours allocated to training and will consist of 2 sessions per week supervised by a physiotherapist (one-on-one) and last 6 months (48 training sessions in total). Each session will last 60, 75 and 90 min during the first, middle and last two months of the training program, respectively. Thus, INT and CON are matched for training time, but the effective training time or volume load (resistance times repetitions) is not controlled. No study restrictions are imposed on potential regular ‘outside-the-study’ visits to physiotherapists or visits from occupational therapists. Acceptable adherence is defined as a completion of minimum 70% of scheduled training sessions. Moreover, number/percent of completed training sessions and achievement of target intensity/volume will be registered in a training log by the physiotherapist. Detailed intervention descriptions can be found in *Additional File 3*.

#### Training teams

At each trial centre the training team will consist of 1–2 physiotherapists to schedule and conduct the training. Moreover, one external physiotherapist will act as an expert consultant to ensure a comparable intervention between sites and physiotherapists. Regardless of experience, physiotherapists will receive training in intervention delivery. A training brochure compiling possible exercises including progressions/regressions will be developed ahead of and updated during the intervention period. The training teams will have weekly-to-biweekly meetings regarding status/progression of study participants and to ensure physiotherapists are adhering to the prescribed intervention. No formal assessment of competences within intervention delivery will be conducted.

#### Trial sites

Two trial centres are established for the present project (Odense and Copenhagen) to ensure the study meets the target sample size with an adequate flow of participants through the study. The trial centre in Odense is affiliated with Odense University Hospital, and the attached training facility is located at the Department of Sport Science and Clinical Biomechanics (University of Southern Denmark). The trial centre in Copenhagen is affiliated with Herlev and Gentofte Hospital and ‘Rigshospitalet’, and the attached training facility is located at the outpatient clinic at “Bodil Eskesen Centret”. Testing and training will run parallel in Odense and Copenhagen with two different training teams. Experiences/knowledge regarding individualisation/progressions will be shared between trial sites to ensure standardisation of intervention delivery. A technician working on the research project will be responsible for the functionality of the robots.

#### Intervention training

The intervention comprises repeated high-intense task-specific practice of functional movement patterns facilitated by dynamic BWU robotic technology including 1) gait training and 2) functional training and therefore aptly titled “robot-assisted training”. The functional training is designed to strengthen the muscles of the lower extremities and features exercises such as sit-to-stand and stair-walking. A detailed description of the intervention and active control-group training can be found in *Additional File 3.* The presently implemented robot yields a dynamic unloading force applied to the body centre of mass, thereby decreasing the requirements for contractile muscle force production [23]. The BWU robot was developed and custom-built at the University of Southern Denmark using a computer-controlled electric motor combined with force and positions sensors [21]. The robot is mounted in ceiling rails and controls a vertical rope to which the participant is attached (*c.f. Additional File 4: The robot and the harness system*). A static safety harness is also attached thereby ensuring no risk of falling during BWU training. The robot only controls the rope and does not provide mechanical support to guide limb movements. No specific training is conducted for the upper extremities in either INT or CON.

#### Active control group training

The active control group comprises repeated high-intense task-specific practice of functional movement patterns without the use of BWU. CON will consist of “standard training”, which is designed to mimic the current practice of training following subacute rehabilitation. The training program has the same functional goals as INT but is conducted without the assistance of the BWU robot thus only relying on manual support from the physiotherapist, relevant walking aids and a walking track with parallel bars. Participants in CON may perform the same exercises as in INT (e.g., gait training using parallel bars, activation exercises, and functional exercises). Intensity and volume will be regulated by adjusting the amount of physical support and the difficulty of the specific exercise.

### Testing procedure

#### Time-points

In accordance with recommendations for a core outcome set of measurements, the included time-points refer the time since onset of stroke [24]. Thus, time points included in the prospective cohort are 3-, 6-, 12-, and 18-months post-stroke (T3, T6, T12 and T18). Onset of stroke (T0) refers to within 3 days of onset of symptoms [24]. Time points included in the RCT are pre-intervention (Pre) and post-intervention (Post). Subsequently, a follow-up will be conducted 6 months after termination of intervention (Follow-up). Time since stroke will be reported with the study findings for the RCT. The primary time point is immediately after 6 months training (Post) (cf. Table 1).

**Table 1 Tab1:** Study Outcomes and Time-Points

**Prospective cohort**	**T3**	**T6**	**T12**	**T18**
IPAQ	x	x	x	x
EQ-5D	x	x	x	x
Fatigue Severity Scale 7	x	x	x	x
Modified Rankin Scale	x	x	x	x
Blood Biomarkers	x			
**RCT**		**Pre**	**Post**	**Follow-up**
**Primary outcome:**				
Fugl-Meyer Lower Extremity Assessment		x	x	
**Secondary outcomes:**				
EQ-5D		x	x	x
Fatigue Severity Scale 7		x	x	x
IPAQ		x	x	x
Modified Rankin Scale		x	x	x
Global Rating of Change			x	x
Barthel Index		x	x	
Berg Balance Scale		x	x	
Functional Ambulation Category		x	x	
10-Meter Walking Test		x	x	
Hand-grip Strength		x	x	
**Other outcomes:**				
Muscle strength		x	x	
Modified Sit-to-Stand Test		x	x	
Modified Ashworth Scale		x	x	
Major Depression Inventory		x	x	
Montreal Cognitive Assessment		x	x	
Oxford Cognitive Screen		x	x	
Blood Biomarkers		x	x	

Patient record data from onset of stroke (T0) and from 3 month post-stroke (T3) will be reported. Additionally, data on comorbidities and pharmacological treatment will also be collected at Pre/Post-intervention to assess any changes in these variables during the intervention period and to ensure study participant do not commence pharmacological treatment leading up to the pre- or post-intervention test days

#### Prospective cohort

Study participants in the prospective cohort will receive three electronic questionnaires: The Fatigue Severity Scale-7 (FSS-7), The EQ-5D-5L and the International Physical Activity Questionnaire (IPAQ) (Patient Reported Outcome Measurements; PROMs). A health professional will draw a blood-sample at 3-months post-stroke.

#### RCT-study

Study participants will report for testing on two days both pre- and post-intervention at the training facility affiliated with each trial site. RCT participants will receive the same electronic questionnaires as the prospective cohort and will be asked to answer these ahead of test-days. Participants are encouraged to complete them with a family member/friend. Participants who do not answer the questionnaires at home will be able to do so either on the first day of testing with the outcome assessor or between the first and second day of testing at home with the assistance of a family member.

The two days of testing comprise a series of clinical assessments, performance-based measurements, cognitive tests, a depression questionnaire, and a blood sample. Descriptive characteristics will also be assessed on the first day of testing (age, sex, height, body weight, living arrangements). Estimated testing time for one test day is 2 h. Body weight, time spent training outside the study, adherence and adverse events will be monitored continuously throughout the intervention period.

A medical student or clinical project therapist will be responsible for outcome assessment and will be trained in conducting each test according to a standard operating procedure. Outcome assessors are required to be certified for drawing blood samples and for conducting the Montreal Cognitive Assessment. No formal qualifications are required for the remaining tests, although outcome assessor will be involved in the aforementioned pilot experiments in order to enhance the data quality. No formal experience with the stroke population is required. Outcome assessors will be provided with written material and oral information regarding stroke symptoms including implications for outcome assessment in the present study.

### Patient records

Patient record data will be extracted from participants upon inclusion for the prospective cohort and RCT with the purpose of providing descriptive characteristics/prognostic factors related to the aetiology of the ischemic stroke. The following data will be collected: Onset of stroke (Date), stroke severity at onset (SSS score), type of stroke (ischemic), stroke confirmed on imaging (yes/no), subtype of stroke (large artery atherosclerosis, small vessel occlusion/lacunar, cardioembolic, other determined aetiology, undetermined), location of infarction, hemisphere containing infract (right/left), paretic leg (right/left), acute treatment (thrombolysis, thrombectomy, bolus of acetylsalicylic acid, bolus of clopidogrel or bolus of acetylsalicylic acid and clopidogrel), blood concentrations of leukocytes, neutrophils, lymphocytes, monocytes, thrombocytes, triglycerides, cholesterol, and C-reactive Protein, mRS at 3 months post-stroke, comorbidities (e.g., heart failure, chronic kidney disease, diabetes, atrial fibrillation), and medication (stroke-specific pharmacological treatment from 3 months before study inclusion to post-intervention). Data on comorbidities and pharmacological treatment will be monitored continuously to assess any changes in these variables during the intervention period.

### Outcome measurements

#### Primary outcome

The primary outcome measurement is the between-group difference in the change score of the Fugl-Meyer Lower Extremity Assessment (FM-LE) from pre- to post-intervention on the intention-to treat population. The FM-LE assesses motor function [27] and has been recommended as a part of a core outcome set in stroke rehabilitation studies [24] and is commonly used in stroke research to evaluate motor recovery due to its clinometric properties [28, 29]. The FM-LE assesses reflex activity, voluntary movement, and coordination and velocity of movement through a 0–34 point ordinal scale with each item scored as: 0 = cannot be performed, 1 = partially performed, and 2 = performed completely [27, 30].

#### Secondary outcomes

Secondary outcomes are the between-group differences in change scores from pre- to post-intervention on the intention-to treat population. The outcomes are described below:

##### Modified Rankin Scale

The mRS is a valid and reliable clinical assessment of global disability widely used in clinical settings and recommended as a part of a core outcome set for stroke trials [24, 31]. It’s a mandatory assessment for all stroke patients in Denmark 3 months post stroke. The patient is asked a series of questions to establish the degree of disability or dependence in daily activities with possible scores ranging from 0-6 where 0 = no symptoms and 6 = deceased.

##### Functional Ambulation Classification

The functional ambulation classification is a valid, reliable, and responsive clinical assessment designed to categorise patients according to gait capacity on a 0–5 ordinal scale: 0) Nonfunctional ambulation, 1) Ambulator—Dependent for Physical Assistance Level II, 2) Ambulator—Dependent for Physical Assistance Level I, 3) Ambulator—Dependent for Supervision, 4) Ambulator—Independent Level Surfaces only and 5) Ambulator – Independent [32, 33].

##### Berg Balance Scale

The Berg Balance Scale is a reliable clinical assessment with 14 items each graded from 0 to 4 rating the patient’s ability to maintain positions of varying difficulty and perform specific tasks such as rising from a chair [34].

##### Gait speed

The 10-m walking test is a performance-based measurement to evaluate gait speed. This test is recommended in two forms as a part of a core outcome set; 1) Can the person independently walk 10 m (gait aids permitted) yes/no? and 2) self-selected gait speed on the 10-m test if the person is able to independently walk 10 m [24].

##### Hand grip strength

Hand-grip strength (kg) is a performance-based measurement assessed using a hand-held dynamometer and used in the present study as an indicator for upper limb function [35].

##### Barthel-100

The Barthel-100 Index is a clinical assessment of independence in activities of daily living (ADLs) through observation [36]. The assessment has 10 items (feeding, bathing, grooming, dressing, bowels, bladder, toilet use, transfers, mobility, stairs) and participants may score 0–100 points. This measurement has been recommended as a part of a core outcome set [37].

##### The International Physical Activity Questionnaire

The IPAQ-Short Form is a patient-reported outcome measurement used to measure physical activity over the past week in four different intensity levels, including 1) vigorous activities, 2) moderate activities, 3) walking, and 4) sitting. Higher values equal higher levels of physical activity.

##### EQ-5D-5L

The EQ-5D-5L (European Quality of Life—5 Dimensions) is a validated survey for measuring health-related quality of life [38]. It consists of five dimensions: mobility, self-care, usual activities, pain/discomfort, and anxiety/depression. The outcome is reported on a scale of 1–5 where 1 is no problems and 5 is extreme problems. This measurement has been recommended as a part of a core outcome set [24].

##### Fatigue Severity Scale 7

The FSS-7 is a one-dimensional 7-item patient-reported outcome measurement commonly implemented in stroke trials. Each item is scored from one to seven with higher scores indicating increased fatigue. The FSS-7 was shown to be more valid than the 9-item version of the instrument (FSS-9) [39, 40], and therefore this version of the instrument is implemented.

##### Global Rating of Change

Global Rating of Change is used to assess the participants' overall experience of change from pre- to post-intervention and from post-intervention to follow-up. A seven-point Likert scale is used. Participants will be asked to compare their current overall health to their health 6 months ago with answers ranging from “Much worse”, “Little worse”, “The same”, “Little better”, and “Much better”.

#### Other exploratory outcomes

##### Modified Sit-to-Stand

This test is a modified version of the classic 5-times performance-based chair rise test. Participants will perform 5 sit-to-stand movements as fast as possible but will be provided with body weight unloading to facilitate a more appropriate movement intensity allowing them to finish within 60 second.

##### Muscle strength

Muscle strength is a performance-based measurement assessed in the present study using handheld dynamometry to test the contractile muscle strength of the lower extremities [41].

##### Modified Ashworth Scale

The Modified Ashworth Scale is clinical assessment of spasticity defined as velocity-dependent exaggeration of stretch reflexes. Clinically this is assessed on a 6-point ordinal scale by moving the joints of the participants through full range of motion at a standardised velocity with ratings ranging from 0 (no increase in tone) to 4 (limb rigid in flexion and extension) [42, 43].

##### Major Depression Inventory

The Major Depression Inventory is a dual function questionnaire (diagnostic tool or rating scale). In the present study it is used as a rating scale to indicate the degree of depression on a scale from 0 (no depression) to 50 (maximum depression) [44].

##### Oxford Cognitive Screen

The Oxford Cognitive Screen (OCS) is a stroke-specific cognitive test with 5 domains: Attention and executive function, language, memory, number processing, and praxis [45]. All tasks are scored individually and can be compared against normative data to determine impairments.

##### Montreal Cognitive Assessment

The Montreal Cognitive Assessment (MoCA) is a dementia screening tool commonly used in clinical trials to screen for cognitive deficits following stroke. The MoCA tests the following cognitive domains and provides a total score from 0–30, where 30 indicates best possible cognitive function: visuospatial abilities, executive functions, short-term memory recall, attention, concentration, working memory, language, and orientation to time and space [46].

##### Blood Biomarkers

Venous blood will be drawn from a vein in the cubital fossa by a health professional and collected in 6 mL EDTA tubes or 4 mL vacutainers at 3-months post-stroke (T3) as well as at pre- and post-intervention. Thus, 3 × 18 ml (= 54 ml blood) will be drawn over the course of approximately 9 months if participants are included in both the cohort and RCT (otherwise 36 ml blood in total for RCT and 18 ml for cohort). Samples will be analysed to determine blood concentrations of neurofilament light chain (NF-L) [47, 48] and glial fibrillary acidic protin (GFAP) [49] and changes in peripheral blood mononuclear cells (PBMCs) [50].

### Adverse Events

Resistance training, functional training and gait training (with or without BWU) are well-established and tolerated interventions in the chronic stroke population [3, 12, 28, 51–53], and the health-related benefits for the study participants justify the initiation of the study. The provided training in the intervention and control group will be carried out by physiotherapists who will ensure safety in training. Additionally, when study participants are body weight unloaded, a static safety harness is attached thereby ensuring no risk of falling during BWU training. All training procedures and measurement methods have previously been implemented in stroke-affected individuals or a similar population.

Adverse events (AEs) may include temporary (passing) experiences of local muscle soreness, shortness of breath, fatigue-induced limitations in activities of daily living following training/testing, falls and fractures, which may or may not be indirectly linked to the research intervention [28]. Additionally, drawing blood samples may cause slight discomfort from the needle. All guidelines regarding sterility etc. is followed, whereby minimal discomfort is associated with the procedure, and the risk of infection is very small. In rare cases a small bruise can occur causing local tenderness around the needle-injection site. Should participants regain enough physical function to attempt standing/walking at home, they may be predisposed to an increased risk of falling at home. Therefore, all study participants will be instructed in safety measures if attempting to stand/walk at home. Generally following stroke, there is a risk of recurrent stroke, myocardial infarction, re-hospitalisation and death [28, 54]. All AEs will be collected as data by the physiotherapists in charge of the training intervention (by asking participants and family members) and through patient records, and these will be reported in the main RCT article. The risks associated with participation in the present study are relatively minor in severity. Considering these risks on their own and in relation to the potential advantages of participating, it seems justifiable to initiate the study.

### Data management

Data will be handled responsible in accordance with the General Data Protection Regulation (GDPR) and the rules on protection of personal data from The Danish Data Protection Agency. The Open Patient data Explorative Network (OPEN) in the Region of Southern Denmark will be responsible for data management. The project will be registered at the internal registry at Region of Southern Denmark. Blood samples will be stored in a research-biobank for the purpose of later analysis and will be destroyed following expiration of project approval with the regional ethics committee.

Study data will be managed using REDCap electronic data capture tools. The electronic questionnaires are automatically sent to participants through e-Boks and will automatically appear in the REDCap database. For the RCT, data will be collected on paper, and outcome assessors will be responsible for data entry to the database. The electronic data base is set up with data entry verification to ensure correct values (proper format and within an expected range). Outcome assessors have restricted access to the database in order to prevent them from viewing data from the pre-intervention data collection, and they will not be able to view randomisation codes to maintain blinding. Data entry is performed locally at each trial site into one common database ensuring data is coded the same way.

### Statistical Analysis

#### Primary Analysis

An assessor-blinded intention-to-treat (ITT) analysis will be performed on primary and secondary outcome measures (Primary Analysis). The ITT analysis will employ a two-way analysis of variance (ANOVA) to analyse between-group differences in change-scores from pre- to post-intervention. No interim analysis will be performed. Full analysis data sets will be created with multiple imputation as part of a sensitivity analysis to examine the robustness of the primary analysis.

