#### Randomisation

The present RCT will use a stratified block randomisation design. Randomisation will be performed internet-based using REDCap Randomise, allocated 1:1. Allocation sequence will be stratified according to global disability (modified Rankin Scale (mRS) score 3, 4 and 5) in blocks of 2 and 4. Stroke-affected individuals will be randomised to robot-assisted dynamic BWU training (INT) or standard training (CON) following pre-intervention testing. The allocation sequence is provided by a data manager with no clinical involvement in the trial, and it is concealed in a password-protected computer file only accessible to the data manager. Participants will be randomised to the intervention group or the active control group by a member of the research team not involved in outcome assessment or statistical analysis.

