#### Secondary analyses

Secondary analyses will employ ANOVA to analyse between-group differences in change-scores in the per-protocol dataset (only including participants demonstrating acceptable adherence of > 70%). Secondary analyses will also be performed to evaluate long-term outcome (follow-up 6 months after post-intervention testing) and to evaluate tertiary outcomes not included in the main RCT manuscript.

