#### Sample size calculation

A priori two-sided sample size calculation for two independent groups was performed and resulted in a required sample size of 34 study participants in total. This was based on detecting a minimally clinically important between-group difference (MCID) of 6 points on the FM-LE scale [55] and a standard deviation of 6 points [28, 30, 55] at an α level of 5% and with a statistical power of 80%. Allowing for dropout the aim is to include 40 participants in total.

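### The primary analysis is a two-way ANOVA on FM-LE change scores that names only one factor and does not use the Pre score as a covariate; ANCOVA would be better defined and more precise

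*Protocol article*

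**What the plan says.** In the protocol article, Statistical Analysis, Primary Analysis: "The ITT analysis will employ a two-way analysis of variance (ANOVA) to analyse between-group differences in change-scores from pre- to post-intervention". The sentence covers the primary and secondary outcomes in the intention-to-treat population. It names no second factor and no covariate.

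The outcome definition agrees with it. Under Primary outcome: "The primary outcome measurement is the between-group difference in the change score of the Fugl-Meyer Lower Extremity Assessment (FM-LE) from pre- to post-intervention". Table 1 marks FM-LE at Pre and Post only: "Fugl-Meyer Lower Extremity Assessment x x".

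Under Secondary analyses, the per-protocol model for the same kind of outcome is called plain ANOVA: "Secondary analyses will employ ANOVA to analyse between-group differences in change-scores in the per-protocol dataset".

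Two design variables could be a second factor. Randomisation says: "Allocation sequence will be stratified according to global disability (modified Rankin Scale (mRS) score 3, 4 and 5) in blocks of 2 and 4". Trial sites says: "Two trial centres are established for the present project (Odense and Copenhagen". Neither section connects its variable to the analysis.

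The sample size section assumes a comparison with one factor: "A priori two-sided sample size calculation for two independent groups was performed and resulted in a required sample size of 34 study participants in total". It uses a difference of 6 points, an SD of 6 points, alpha 5% and power 80%, and raises the total to 40 for dropout. It does not say whether the SD is that of change or of scores at one visit.

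**The concern.** There are two linked problems.

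**The model is not identified by its own description.** A two-way ANOVA needs two factors. With one change score per person, time has already been used up in the subtraction and cannot be the second. Group by mRS stratum, group by site, and a group-by-time analysis of the raw scores are all possible meanings. The per-protocol sentence drops the word two-way for the same change scores, so the article does not settle which is meant. In a trial of 40 people, the choice of factors should not remain open once outcome data are available.

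**The stated handling of baseline is inefficient.** A change score fixes the coefficient of Pre at 1, whatever the data say. When Pre and Post correlate imperfectly, that over-corrects. The estimate carries avoidable noise, and an arm that happens to start lower tends to look better through regression to the mean. ANCOVA estimates the coefficient and removes both effects, using a measurement that is already scheduled for every participant.

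What is at stake is the precision of the primary answer in a trial planned with little power to spare.

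**Working it through.** **Inputs from the article.** Difference 6, SD 6, two-sided alpha 0.05, power 80%, total 34 (Sample size calculation); equal allocation (Randomisation: "Randomisation will be performed internet-based using REDCap Randomise, allocated 1:1"). **Assumptions.** The Pre-Post correlation r is not given, so a range is shown. Pre and Post variances are taken as equal. SD 6 is first read as the SD of change.

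**Step 1: reproduce the planned size.** For a two-sample t test, the noncentrality is 6 / (6 × √(2/n)) with 2n − 2 degrees of freedom.
- n = 16 per arm: noncentrality 2.83, power 78.1%.
- n = 17 per arm: noncentrality 2.92, power 80.7%.

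So 17 per arm, 34 in total, is confirmed. The implied dropout is 1 − 34/40 = 15%. The calculation contains no second factor and no covariate.

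**Step 2: variance of the two estimators.** With SD σ at each visit:
- change score: 2σ²(1 − r)
- ANCOVA residual: σ²(1 − r²)
- ratio, ANCOVA to change: (1 + r)/2, which is below 1 for every r below 1.

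**Step 3: power at 17 per arm.** The ANCOVA residual SD is 6 × √((1 + r)/2), with 34 − 3 = 31 degrees of freedom.

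| r | Variance ratio | ANCOVA SD | ANCOVA power | Change-score power | Total N for 80% with ANCOVA |
|---|---|---|---|---|---|
| 0.5 | 0.75 | 5.20 | 90.3% | 80.7% | 26 |
| 0.7 | 0.85 | 5.53 | 86.5% | 80.7% | 30 |
| 0.8 | 0.90 | 5.69 | 84.5% | 80.7% | 32 |
| 0.9 | 0.95 | 5.85 | 82.6% | 80.7% | 32 |

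Adding the three-level mRS stratum takes two more degrees of freedom (29 left). With no credit for any variance that it explains, power becomes 90.2%, 86.4% (0.8635), 84.4% and 82.4%. The cost is about 0.1 to 0.2 percentage points.

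**Step 4: the other reading of SD 6.** If 6 is the SD at a single visit, the change SD is 6 × √(2(1 − r)) and the ANCOVA SD is 6 × √(1 − r²). Power at 34, change score against ANCOVA:
- r = 0.3: 66.6% against 84.1%
- r = 0.5: 80.7% against 90.3%
- r = 0.7: 95.4% against 97.7%

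ANCOVA has the higher power at each of these values.

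**Step 5: chance imbalance.** Given a Pre difference D between arms, the change-score contrast is shifted by −(1 − r)D. Per point of imbalance that is 0.5, 0.3 and 0.1 points at r = 0.5, 0.7 and 0.9.

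The likely size of D needs a baseline SD, which the article does not give. To stay consistent with an SD of change of 6, the baseline SD must be 6/√(2(1 − r)):
- r = 0.5: baseline SD 6.00; standard error of D = 6.00 × √(2/17) = 2.06; shift for a one-standard-error imbalance = 0.5 × 2.06 = 1.03 points.
- r = 0.7: baseline SD 7.75; standard error 2.66; shift = 0.3 × 2.66 = 0.80 points.

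If the baseline SD is instead held at 6, the shift at r = 0.7 is 0.3 × 2.06 = 0.62 points. The target difference is 6.

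**The case against.** **The analysis plan is announced but not shown, and may name the factors.** It may. Leaving factors and covariates to that document is normal practice, and silence alone would be no finding. But the article is not silent: it fixes a named method and a named outcome that do not determine a model together, and it chooses change scores. If the analysis plan already resolves this, the sponsor need only confirm it and record the departure from the article.

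**Two-way could be perfectly sound.** Group by mRS stratum, or group by site, on change scores is a valid two-way ANOVA with one value per person. This stands: the second factor is unnamed, not shown to be absent. Either version would still leave Pre FM-LE out as a covariate.

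**The change-score contrast is valid.** This also stands. Randomisation makes it unbiased on average, and the planned 34 is right for it if 6 is the SD of change. Stratifying on mRS may limit imbalance in severity, and at high r the gain from ANCOVA is small.

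**Stronger readings that the article does not support.**
- A reader might infer that the baseline score is ignored. It is not, because it is subtracted.
- A reader might take group by time as the model and conclude that the group main effect would answer the wrong question, or that Pre and Post rows would be treated as independent. The article prescribes neither. It targets differences in change, which correspond to the interaction, and with two visits a proper repeated-measures interaction test is the same as the change-score t test.
- A reader might expect a ceiling at the scale maximum of 34 to worsen matters. No baseline FM-LE distribution is given, so this is not shown.

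**Conclusion.** The concern holds as one of specification and efficiency. As written, the primary model names one factor where two are required, and it adjusts for Pre only by subtraction. It does not make the trial's answer invalid.

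If SD 6 is the SD of change, the gain forgone is about 10 percentage points of power at r = 0.5, 6 at r = 0.7 and 2 at r = 0.9. A one-standard-error chance imbalance at Pre would move the unadjusted estimate by roughly 0.6 to 1.0 points at r between 0.5 and 0.7. These figures rest on an assumed r, equal Pre and Post variances, 17 analysed per arm and, for the imbalance, an assumed baseline SD. That ANCOVA has the smaller variance does not depend on which r below 1 applies. The change is worth making because it is nearly free.

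**What to change.** In the statistical analysis plan, before the primary analysis is run and therefore before unblinding, replace the two-way ANOVA with ANCOVA. Regress Post FM-LE on randomised group, with Pre FM-LE as a covariate and the mRS randomisation stratum (3, 4, 5) as a factor. Report the adjusted mean difference with its 95% confidence interval. Using the change score as the dependent variable in the same model gives an identical group estimate, so the primary outcome definition can stay as it is.

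Use the same model, with the matching Pre value, for the continuous secondary outcomes and for the per-protocol set. Record the change as a departure from the published article, and state whether the planning SD of 6 is that of change or of a single visit.

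The cost is a short passage of text and three degrees of freedom (one for Pre, two for the stratum). No new data, visits or participants are needed.
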